## Abstract

**Background:**

The Acute Respiratory Distress Syndrome (ARDS) is a common cause of respiratory failure in critically ill patients. Experimental studies suggest that treatment with beta agonists may be helpful in ARDS. The Beta Agonist Lung Injury TrIal (BALTI-2) is a multicentre, pragmatic, randomised, double-blind, placebo-controlled clinical trial which aims to determine if sustained treatment with intravenous (IV) salbutamol will improve survival in ARDS.

**Methods/Design:**

Patients fulfilling the American-European Consensus Conference Definition of ARDS will be randomised in a 1:1 ratio to receive an IV infusion either of salbutamol (15 μg kg ideal body weight^-1 ^hr^-1^) or placebo (0.9% sodium chloride solution), for a maximum of seven days. Allocation to randomised groups will use minimisation to ensure balance with respect to hospital of recruitment, age group (<64, 65-84, >85 years) and PaO_2_/FiO_2 _ratio (≤6.7, 6.8- 13.2, ≥13.3 kPa). Data will be recorded by participating ICUs until hospital discharge, and all surviving patients will be followed up by post at six and twelve months post randomisation. The primary outcome is mortality at 28 days after randomisation; secondary outcomes are mortality in ICU, mortality in hospital, number of ventilator-free days, number of organ failure-free days, mortality at twelve months post-randomisation, quality of life at six and twelve months, length of stay in ICU, length of stay in hospital, adverse effects (tachycardia, arrhythmia or other side effects sufficient to stop treatment drug). 1,334 patients will be recruited from about fifty ICUs in the UK. An economic evaluation will be conducted alongside the trial.

**Trial Registration:**

Current Controlled Trials ISRCTN38366450.

## Background

The acute respiratory distress syndrome (ARDS) is a condition characterised by a failure of pulmonary oxygen exchange due to increased alveolar-capillary permeability and resultant lung oedema [1]. It can be caused by primary lung conditions such as aspiration, pneumonia, or can arise as a complication of non-pulmonary conditions such as severe sepsis. ARDS is defined by the 1994 American-European Consensus Conference [2] as the acute onset of hypoxaemia (PaO_2_:FiO_2 _ratio of < 200mm Hg), bilateral infiltrates on a chest radiograph in the absence of cardiogenic causes of pulmonary oedema.

ARDS is common, The ALIVE study reported 13.3% of patients who require mechanical ventilation have ARDS [3]. Intensive Care Unit (ICU) mortality is estimated at 41-46%, corresponding to about 2,200 deaths per year in the UK [4,5]. Patients with ARDS consume significantly more resources than matched patients without ARDS since they require a longer ICU and hospital stay (median 17 vs 8 days and 31 vs 25 days, respectively) [3], and convalescence on the ward and subsequent rehabilitation in the community. The quality of life after ARDS is significantly reduced with 35% unable to return to work 24 months after hospital discharge [6,7]. ARDS has no primary pharmacological treatments proven to improve outcome other than supportive care with a lung-protective ventilator strategy [8].

Laboratory studies over the last 20 years suggest a potential therapeutic role for β_2 _agonists in ARDS [9]. In brief, evidence suggests these agents reduce alveolar inflammation [10,11], improve endothelial/epithelial barrier function [12,13], accelerate alveolar fluid clearance [14] and enhance epithelial repair [13,15]. A single centre phase 2 trial (Beta Agonist Lung Injury TrIal-1; BALTI-1) investigated the efficacy of intravenous salbutamol on *in-vivo *fluid clearance through serial measurement of extra-vascular lung water in 40 patients with ARDS [16]. The study demonstrated that a sustained intravenous infusion of salbutamol (15 μg kg ideal body weight^-1 ^hr^-1^) over 7 days significantly reduced lung water (day 7 lung water mean (SD), 9.2 (6) vs 13.2 (3) ml kg^-1^, P = 0.038) and plateau airway pressures (23.9(3.8) vs 29.5(7.2) cm H_2_O, P = 0.049). This study provided proof of concept that treatment with intravenous beta agonists may influence alveolar fluid clearance. The study lacked sufficient power to measure the effect on other clinical and cost effectiveness outcomes. The BALTI-2 trial was conceived to test the hypothesis that sustained treatment with intravenous beta agonists in ARDS would improve 28 day mortality and other clinical and cost effectiveness outcomes.

## Methods/Design

### Trial Summary

BALTI-2 is a multicentre, pragmatic, randomised, double-blind, placebo-controlled clinical trial. Patients fulfilling the American-European Consensus Conference Definition of ARDS will be randomised in a 1:1 ratio to receive an IV infusion either of salbutamol (15 μg kg ideal body weight^-1 ^hr^-1^) or placebo (0.9% sodium chloride solution), for a maximum of seven days. Allocation to randomised groups will use minimisation to ensure balance with respect to hospital of recruitment, age group (<64, 65-84, >85 years) and PaO_2_/FiO_2 _ratio (≤6.7, 6.8- 13.2, ≥13.3 kPa). The trial will be fully blinded and all drugs will be packaged identically, so that patients, clinicians or investigators will not know which patients are in each arm. Data will be recorded by participating ICUs until hospital discharge, and all surviving patients will be followed up by post at six and twelve months post randomisation. The primary outcome is mortality at 28 days after randomisation; secondary outcomes are mortality in ICU, mortality in hospital, number of ventilator-free days, number of non-pulmonary organ failure-free days, mortality at twelve months post-randomisation, quality of life at six and twelve months, length of stay in ICU, length of stay in hospital, adverse effects (e.g. tachycardia, arrhythmia, lactic acidosis). 1,334 patients will be recruited from about fifty ICUs in the UK, and an economic evaluation will be conducted alongside the trial.

### Approvals

The trial is approved by Oxfordshire REC "A" (06/Q1604/123) and MHRA CTA number 24698/0004/001 and EudraCT Number: 2006-002647-86. The trial is registered on the International Standard Randomised Controlled Trial Registry (ISRCTN38366450). The trial is co-sponsored by the University of Warwick and Heart of England NHS Foundation Trust (http://www.heartofengland.nhs.uk/ ). The trial is being coordinated by the Warwick Clinical Trials Unit (http://www.warwick.ac.uk/go/ctu). The trial is funded by the Medical Research Council (MRC) and will be conducted in accordance with Good Clinical Practice Guidelines, applicable UK Clinical Trials Regulations and the Standard Operating Procedures of the Warwick Clinical Trials Unit. The trial will be reported in line with the Consolidated Standards of Reporting Trials (CONSORT) 2010 guidelines [17].

### Outcome measures

#### Efficacy

The primary outcome of the study is all cause mortality 28 days after randomisation. Secondary outcomes are mortality before (first) discharge from ICU; mortality before (first) discharge from hospital; number of ventilator-free days; number of non-pulmonary organ failure-free days; duration of ICU and hospital stay; health related quality of life and mortality at twelve months post randomisation.

Ventilator free days were defined in accordance with the ARDSnet criteria [18] as the number of calendar days after initiating unassisted breathing to day 28 after randomisation, assuming a patient survives for at least 48 consecutive hours after initiating unassisted breathing. Un-assisted breathing is defined as one of at least 48 consecutive hours of (1) being extubated with face mask, nasal prong oxygen, or room air (2) T-tube breathing (3)Tracheostomy mask breathing, CPAP = 5 cm H_2_0 without pressure support of intermittent mandatory ventilation assistance.

Non-pulmonary organ failure-free days are defined as the number of days in the first 28 days after randomization that the patient has none of: respiratory support, cardiovascular support, renal support, or neurological support. Organ failure was defined according to Critical Care Minimum Dataset definitions [19].

#### Safety

The frequency with which the following events occur will be reported (1) tachycardia sufficient to stop treatment with trial drug (2) new arrhythmia sufficient to stop treatment with trial drug (3) other side effects sufficient to stop treatment with trial drug (4) serious adverse events and suspected unexpected serious adverse reactions.

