#### Alteration of Infusion Rate

Sinus tachycardia or arrhythmias are known side effects of intravenous salbutamol administration. If a patient receiving a trial drug infusion is noted to have tachycardia (heart rate > 140 beats min^-1^) or any new arrhythmia occurs, the dose rate of drug will be adjusted according to the flow diagram (figure 1). Dose adjustments for renal or hepatic failure will be driven by the cardiovascular response to the infusion rather than on the degree of renal or hepatic impairment. Standard anti-arrhythmic therapy will be given if indicated in addition to alteration of infusion rate.

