#### Infusion Termination Criteria

Termination of the infusion is defined as discontinuation of the trial drug infusion without intention to restart the infusion at a later time. Trial drug infusion will be terminated in the following circumstances: death; heart rate >140 beats min^-1 ^despite two adjustments in infusion rate; new arrhythmias despite adjustment in infusion rate; development of a significant lactic acidosis, which in the opinion of the treating clinician is attributable to infusion of the trial drug; 24 hours after discontinuation of mechanical ventilation (of any sort); discharge from ICU; discontinuation of active treatment; request to withdraw from the personal or professional legal representative; decision by the attending clinician that the infusion should be discontinued on safety grounds; 7 days (168 hours) after randomization.

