### Adverse Event Management

BALTI-2 is recruiting a population that is already in a life-threatening situation, it is therefore expected that many of the participants will experience serious adverse events. Events that are expected in this population and those that are collected as outcomes (e.g. death, organ failure) of the trial will not be reported as SAEs. Other SAEs or SUSARs that occur between trial entry and 30 days after the end of the trial drug infusion will be reported by faxing a serious adverse event log to the trial co-coordinating centre.

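### Tachycardia and arrhythmia controlled by a rate change fall outside the named safety outcomes, whose definition varies within the article; a smaller point is that the SAE window varies by patient

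*Protocol article*

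**What the plan says.** All references are to the protocol article.

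- **Outcome measures, Safety.** Four frequencies will be reported. The first two are "tachycardia sufficient to stop treatment with trial drug (2) new arrhythmia sufficient to stop treatment with trial drug". The third is "3) other side effects sufficient to stop treatment with trial drug". The fourth, "4) serious adverse events and suspected unexpected serious adverse reactions", carries no stopping condition.
- **Alteration of Infusion Rate.** Sinus tachycardia and arrhythmias are acknowledged effects of intravenous salbutamol. If the heart rate exceeds 140 per minute or a new arrhythmia occurs, "the dose rate of drug will be adjusted according to the flow diagram".
- **Infusion Termination Criteria.** Tachycardia ends the infusion if it persists "despite two adjustments in infusion rate"; a new arrhythmia ends it if it persists after adjustment. The infusion also ends at, among other points, death, attributable lactic acidosis, 24 hours after mechanical ventilation stops, ICU discharge, or 168 hours after randomisation.
- **Adverse Event Management.** For SAE reporting, the rule is that "Events that are expected in this population and those that are collected as outcomes (e.g. death, organ failure) of the trial will not be reported" in that way. The remaining SAEs and SUSARs are reported if they fall "between trial entry and 30 days after the end of the trial drug infusion".
- **Trial Summary and Statistical Analysis.** Both name tachycardia and arrhythmia without the stopping condition. The Trial Summary adds lactic acidosis as an example. The Statistical Analysis section plans risk ratios for tachycardia, arrhythmia and other side effects. The Abstract does carry the condition, although its grammar leaves open whether it applies to all three terms or only to the last.

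**The concern.** The two cardiac outcomes record events that management failed to control rather than events that occurred. For a drug with acknowledged cardiac effects, the frequency of tachycardia and arrhythmia needing a response is basic harm information, and the article fixes an outcome that leaves part of it out. A reader of the final report could also take a risk ratio labelled arrhythmia to cover all new arrhythmia when it covers only arrhythmia that ended treatment.

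The second, lesser worry is that SAE observation ends at a time set by something that happens after randomisation and that treatment can influence. The arms may then be observed for different lengths of time.

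**Working it through.** **1. Which events reach the safety outcomes.** The article gives no figure to reproduce here, so the sections are followed through case by case.

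| Event | Items 1–2 | Item 4 (SAE/SUSAR) |
|---|---|---|
| Heart rate >140, settles after one or two rate adjustments | Not counted | Only if serious and not treated as expected or as a trial outcome |
| New arrhythmia, settles after adjustment | Not counted | Same |
| Either event, persists and stops the infusion | Counted | Same |

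The Adverse Event Management exclusion matters for the last column. Tachycardia and arrhythmia could be classed as expected in this population, or as events already collected as outcomes. A serious arrhythmia controlled by a rate change could then be missing from both places.

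**2. What this does to the comparison.** Let *c* be the proportion of events in an arm that are controlled by a rate change. Then:

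counted RR = true RR × (1 − *c*, salbutamol) / (1 − *c*, placebo)

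If *c* is equal in the two arms, the ratio is unchanged, but the counts and the absolute difference shrink. If *c* is higher on salbutamol, the counted ratio is too low. That is plausible, because lowering the rate of a saline infusion cannot relieve a drug effect. It remains inference, since the article gives no value for *c* in either arm.

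**3. Definitions side by side.**

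| Place | Stopping condition on tachycardia and arrhythmia | Lactic acidosis named as an adverse effect |
|---|---|---|
| Abstract | Yes (grammar ambiguous) | No |
| Trial Summary | No | Yes |
| Outcome measures, Safety | Yes | No |
| Statistical Analysis | No | No |

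**4. Length of the SAE window.** The inputs are the infusion's latest end, 168 hours after randomisation (168 / 24 = 7 days), and the 30-day extension. For an infusion ending at day *d* after randomisation, the window ends at day *d* + 30.

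- *d* = 7: 7 + 30 = 37 days.
- *d* = 3: 33 days, (37 − 33) / 37 = 10.8% shorter.
- *d* = 1: 31 days, 6 / 37 = 16.2% shorter.
- *d* → 0: 30 days, 7 / 37 = 18.9% shorter.
- Infusion never started (the Drug supply section delays the start while heart rate exceeds 140): no end date is defined.

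**5. How much the window could matter.** The article gives no SAE or stopping rates, so the following is illustration only. Assume no true difference, a constant hazard, a 37-day SAE risk *p*, all placebo infusions running 7 days, and a fraction *f* of salbutamol infusions stopping at day 1. With λ = −ln(1 − *p*) / 37,

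apparent RR = [*f* × (1 − exp(−31λ)) + (1 − *f*) × *p*] / *p*

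For *p* = 0.10 and *f* = 0.30: λ = 0.10536 / 37 = 0.002848; 1 − exp(−0.08828) = 0.0845; RR = (0.30 × 0.0845 + 0.70 × 0.10) / 0.10 = 0.95.

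Over *p* from 0.05 to 0.20:

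- *f* = 0.10: about 0.98.
- *f* = 0.30: 0.95 to 0.96.
- *f* = 0.50: 0.92 to 0.93.

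With *p* = 0.10, *f* = 0.30 and a hazard five times higher in the first 7 days, the result is 0.97.

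**The case against.** Stopping trial drug is a clinically meaningful tolerability threshold in intensive care, and double-blinding protects how it is applied. That stands, and it is why the present outcomes should be kept. It does not make them a measure of how often the events occur.

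The wording leaves room on what counts as stopping. The article defines termination as discontinuation without intent to restart, but the Safety section speaks of stopping, which might include a temporary halt, and the flow diagram is not available in the text reviewed. This also stands. On either reading, an event handled by a rate reduction alone is outside items 1 and 2.

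Two stronger readings are tempting. A reader might infer that the safety outcomes capture only events that stop the infusion. They do not: item 4 reports SAEs and SUSARs without that condition. A reader might also infer that harm is under-counted most in the arm whose infusions stop early. For items 1 to 3 the reverse applies, because events that stop the infusion are the ones counted and the loss is among patients who are adjusted and continue.

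For the SAE window, early stopping does shorten observation, but the article does not establish which arm is affected more. Intolerance would shorten windows on salbutamol, and so would earlier extubation or ICU discharge if the drug works; other reasons for ending the infusion can act in either arm. Every infused patient is covered for at least 30 days from randomisation, which spans the whole infusion and the 28-day primary period. Death and organ failure are collected separately on clocks that start at randomisation. The article plans to report SAE frequency and does not list SAEs among its risk ratios. A window of fixed length after exposure is also a common and defensible choice.

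Recording of rate changes and the list of expected events may well sit in the full protocol, so their absence here is not criticised.

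**Conclusion.** The point holds in a limited form, as a cheap improvement rather than a threat to the trial's conclusions.

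- **Main part.** Tachycardia and new arrhythmia controlled by a rate change are not counted in safety items 1 and 2, and those that are non-serious or classed as expected are not recovered through SAE reporting. The article's statements of these outcomes disagree. This follows from the text without assumptions. The number of events involved, and any differential loss between arms, cannot be derived from the article.
- **Secondary part.** The SAE window varies from 30 to 37 days after randomisation according to a post-randomisation event, and is undefined for a patient who never starts. The difference is at most 7 days. Its effect is modest (apparent risk ratios of about 0.92 to 0.98 when 10% to 50% of one arm stops at day 1, on assumed rates), and its net direction is not established.

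**What to change.** 1. **Add one by-arm safety report:** patients with tachycardia above the protocol's own threshold, or with new arrhythmia, leading to any rate reduction, interruption or stop. Keep the present outcomes, limited to events sufficient to stop trial drug, as a stated subset.
2. **Reconcile the definitions** in the Abstract, Trial Summary, Safety and Statistical Analysis sections. Say which version the planned risk ratios use, whether stopping includes a temporary halt, and whether lactic acidosis is an outcome in its own right or falls under other side effects.
3. **Use one SAE window of 37 days from randomisation for everyone** (7 + 30). It covers every current window, makes the difference in window length zero, and defines the end for patients whose infusion never starts.

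The cost is added tabulation, wording changes, and up to 7 more days of SAE reporting for patients whose infusion ends early. Item 1 assumes that rate changes and their reasons are recorded on the case report form; if they are not, a field is needed. Dosing and patient management do not change.

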#### Others

Health related quality of life will be measured using EQ-5D and SF-12 at six and twelve months after randomisation. Resource use including length of ICU and hospital stay; health service contacts up to twelve months after randomisation; out of pocket expenditure and time away from work.

### Eligibility Criteria

Ventilated patients will be screened daily for the development of ARDS. Adult (age > 16) patients are eligible to be included if they are intubated and ventilated within 72 hours of onset of ARDS. ARDS is defined in accordance with the American-European consensus conference definition of acute onset of severe hypoxaemic respiratory failure (PaO_2_/FiO_2 _ratio ≤ 26.7 kPa) with bilateral infiltrates on the chest radiograph in the absence of clinical evidence of left atrial hypertension. Patients will be excluded if they are known to be pregnant; are receiving current treatment with intravenous β_2_-agonists or have a requirement for on-going regular nebulised/inhaled β_2_-agonists; are being treated with β-adrenergic antagonists ("β-blockers"); treatment withdrawal is imminent; chronic liver disease, defined as Child-Pugh grade C; enrolled in another clinical trial of an investigational medicinal product in the last 28 days;

### Consent

Consent will be sought from the patients themselves if this is possible, but it is recognised that in the majority of cases patients will be unable to give informed consent due to alterations in their level of consciousness caused by illness and therapeutic sedation. In this situation informed consent will be sought from a Personal Legal Representative or Professional Legal representative. Retrospective consent/consent to continue will be sought from surviving patients enrolled through consent from a personal/professional legal representative.

### Randomisation

Randomisation will occur via a central telephone randomization service (University of Aberdeen). Randomisation will be minimised by centre, PaO_2_/FiO_2 _ratio (≤6.7, 6.8 to 13.2, ≥13.3kPa), and age (<64, 65 to 84, ≥85 years) because of the expected differences in mortality among these strata. The randomisation service will allocate a numbered treatment pack to each patient. This pack will contain all drugs for giving a complete course of trial treatment to one patient.

### Drug supply

Drug treatment packs containing sealed and blinded glass ampoules of salbutamol sulphate (GlaxoSmithKline) 5 mg in 5 ml or sodium chloride Injection BP 0.9% w/v (Hameln Pharmaceuticals Ltd) will be supplied by Bilcare GCS (Europe) Limited ([name]). All trial drugs will be packaged identically and identified only by number.

Drug infusions will be administered through a dedicated intravenous line at a rate of 0.075 ml (kg ideal body weight)^-1 ^hour^-1 ^(equivalent to 15 μg salbutamol(kg ideal body weight)^-1 ^hour^-1^) according to the patients height (table 1). Trial drug infusions should be started immediately after randomisation. If at the time of attempting to commence the trial drug the patient's heart rate exceeds 140 beats min^-1^, the administration should be delayed until the heart rate is less than 140 beats min^-1 ^for at least 30 minutes. Every attempt should be made to complete the treatment infusion without interruption for a maximum of seven days (i.e. until 168 hours after randomisation).

**Table 1 T1:** Infusion rate according to height (ideal body weight)

Height (cm)	Male IBW (kg)	Infusion Rate (ml hr^-1^)	Female IBW (kg)	Infusion Rate (ml hr^-1^)	Height (cm)	Male (IBW) (kg)	Infusion Rate (ml hr^-1^)	Female IBW (kg)	Infusion Rate (ml hr^-1^)
**146**	44.2	3.3	39.7	3.0	**174**	69.7	5.2	65.2	4.9

**148**	46.0	3.5	41.5	3.1	**176**	71.5	5.4	67.0	5.0

**150**	47.8	3.6	43.3	3.2	**178**	73.3	5.5	68.8	5.2

**152**	49.6	3.7	45.1	3.4	**180**	75.1	5.6	70.6	5.3

**154**	51.5	3.9	47.0	3.5	**182**	76.9	5.8	72.4	5.4

**156**	53.3	4.0	48.8	3.7	**184**	78.8	5.9	74.3	5.6

**158**	55.1	4.1	50.6	3.8	**186**	80.6	6.0	76.1	5.7

**160**	56.9	4.3	52.4	3.9	**188**	82.4	6.2	77.9	5.8

**162**	58.7	4.4	54.2	4.1	**190**	84.2	6.3	79.7	6.0

**164**	60.6	4.5	56.1	4.2	**192**	86.0	6.5	81.5	6.1

**166**	62.4	4.7	57.9	4.3	**194**	87.9	6.6	83.4	6.3

**168**	64.2	4.8	59.7	4.5	**196**	89.7	6.7	85.2	6.4

**170**	66.0	5.0	61.5	4.6	**198**	91.5	6.9	87.0	6.5

**172**	67.8	5.1	63.3	4.7	**200**	93.3	7.0	88.8	6.7

